### Screening visit

The screening visit will determine a subject’s suitability to participate in the study. This visit will last approximately 4 hours and will include;

- Obtaining written informed consent
- Full medical including medical history and prior medication
- ECG
- Demographics
- Clinical laboratory blood testing including capillary blood glucose
- Vitals, alcohol breath test and urine drug screen

Once enrolled into the study, subjects will be asked to monitor CBG twice a day, fasting before breakfast and before dinner for 1 week before the first visit to establish a mean baseline fasting CBG level. The glucose values will be recorded and reviewed daily with a study coordinator by telephone.

### Study Visits

Visit 1

Within approximately 30 days of screening, eligible subjects who provide informed consent will attend the unit for the first study visit lasting approximately 30 hrs. This visit serves as a baseline session during which the following will occur, (see time and events Section 4.4 and Section 7 for details);

- Routine admission assessments
- Blood glucose diary review
- Pharmacodynamic blood sampling for entero-endocrine peptide profiling, serum bile acid and lipid profile
- Faecal collection (bile acids)
- Enterotest duodenal bile collection (bile acids)

Subjects will be admitted to the unit on the late afternoon / evening before PD profiling is due to start. They will be given a standard meal at approximately 6pm and then fasted, except water, from 10pm onwards. At approximately 12am, patients will be asked to swallow the EnteroTest, and the string will remain in situ overnight. The following morning PD blood sampling will begin, followed by the administration of a food cue to trigger gall bladder contraction, the resulting bile being collected by the string, which will be removed 1 hour later. Following initial assessments and testing, metformin will be dosed with a breakfast served at approximately 8am. Further assessments will be timed from the beginning of this meal and are detailed in Section 4.4. The assessments and procedures carried out in each of the 4 study visits will be the same.

Visit 2

Following discharge from the unit post Visit 1, patients will refrain from taking metformin. They will closely monitor their CBG each morning fasting before breakfast and before dinner, continuing to record it in a diary card. Approximately 7 days later they will return for study visit 2. Pharmacodynamic samples, faecal and bile acid collections will be repeated according to the schedule detailed in Section 4.4.

Visit 3

On discharge patients will continue to abstain from metformin and once their mean CBG increases by approximately 25%, from baseline (based on the 7 day average of fasting CBG before Visit 1) or approximately three weeks from the beginning of wash-out, they will be informed by the study co-ordinator to attend for Visit 3. Pharmacodynamic samples, faecal and bile acid collections will be repeated according to the schedule detailed in Section 4.4.

Visit 4

Upon discharge from Visit 3, subjects will resume their usual prescribed dose of metformin treatment and return to the unit for study Visit 4 once their fasting CBG returns to their baseline level (approximate) or achieve clinically acceptable gycaemic control, as determined by the principal investigator. Pharmacodynamic samples, faecal and bile acid collections will be repeated according to the schedule detailed in Section 4.4.

## Treatment Assignment

All subjects will be assigned to an identical regimen in accordance with the treatment schedule outlined in Section 4.1.

### Dose Adjustment/Stopping Efficacy Criteria

Glucose withdrawal criteria will be implemented to ensure subject safety during withdrawal of the metformin treatment. Patients will be required to measure CBG levels from the start of the study at screening until the end of the study. Patients will be withdrawn from the study if their morning fasting blood glucose concentration is above15.0 mmol/L (270mg) for 2 consecutive days.

## Time and Events Table

| Procedure | Screening  (up to 30 days prior to Day 1) |  | Study Day (each visit 1-4) | | | | | | | | | | | | | | | | | | Follow-up  (10-14 days post-last dose) |
| --- | --- | --- | --- | --- | --- | --- | --- | --- | --- | --- | --- | --- | --- | --- | --- | --- | --- | --- | --- | --- | --- |
|  |  | Day  -1 | |  | Day 1 | | | | | | | | | | | | | | | |  |
|  |  |  |  | Pre-breakfast | | 0 h | 30 min | 1 h | 2 h | | 4 h | 4 h30min | 5 h | 6 h | 8h | 9h | 10 h | 10h30min | 11hr | 12 h |  |
| Admission to Unit |  | X | |  | |  |  |  |  | |  |  |  |  |  |  |  |  |  |  |  |
| Informed Consent | X |  | |  | |  |  |  |  | |  |  |  |  |  |  |  |  |  |  |  |
| Demographics | X |  | |  | |  |  |  |  | |  |  |  |  |  |  |  |  |  |  |  |
| Full Physical Exam | X |  | |  | |  |  |  |  | |  |  |  |  |  |  |  |  |  |  |  |
| Brief Physical Exam |  | X | |  | |  |  |  |  | |  |  |  |  |  |  |  |  |  |  |  |
| ECG | X |  | |  | |  |  |  |  | |  |  |  |  |  |  |  |  |  |  | X |
| Medical/medication/ drug/alcohol history | X |  | |  | |  |  |  |  | |  |  |  |  |  |  |  |  |  |  |  |
| Vital signs | X | X | |  | |  |  |  |  | |  |  |  |  |  |  |  |  |  |  | X |
| Serum β-hCG (women) | X | X | |  | |  |  |  |  |  | |  |  |  |  |  |  |  |  |  | X |
| Prior/Con Med review | X |  | |  | |  |  |  |  |  | |  |  |  |  |  |  |  |  |  | X |
| Clinical Lab Bloods | X |  | | X | |  |  |  |  | |  |  |  |  |  |  |  |  |  |  |  |
| Entero-Test ingestion |  | X | |  | |  |  |  |  | |  |  |  |  |  |  |  |  |  |  |  |
| Drink 500ml water |  | X | |  | |  |  |  |  | |  |  |  |  |  |  |  |  |  |  |  |
| Food Cue |  |  | | X | |  |  |  |  | |  |  |  |  |  |  |  |  |  |  |  |
| Remove Bile string |  |  | | X | |  |  |  |  | |  |  |  |  |  |  |  |  |  |  |  |
| Blood Glucose (Cap) Monitoring | X | X | | X | |  |  |  |  | |  |  |  |  |  |  |  |  |  |  | X |
| Pharmacodynamic Blood Sampling^1^ |  | X | | X | | X | X | X | X | | X^4^ | X | X | X |  |  | X^4^ | X | X | X |  |
| Urine Drug/Alcohol Breath | X | X | |  | |  |  |  |  | |  |  |  |  |  |  |  |  |  |  |  |
| Faeces Collection^2^ |  | X | | 🡨-------------------------------------------------------------------------------------------------------------🡪 | | | | | | | | | | | | | | | | |  |
| Meal |  | X | |  | | X |  |  |  | | X |  |  |  |  |  | X |  |  |  |  |
| Discharge^3^ |  |  | |  | |  |  |  |  | |  |  |  |  |  |  |  |  |  | X |  |
| Outpatient Visit | X |  | |  | |  |  |  |  | |  |  |  |  |  |  |  |  |  |  | X |
| Continued | | | | | | | | | | | | | | | | | | | | | |

4.4 Time and Events Table (continued)

| 1. Sample collection times are approximate and may vary as testing dictates 2. A single or all faecal samples passed may be taken over the duration of each study visit. If the patients do not have any bowel movement during their visit, their first faecal sample passed after discharge will be collected at home and shipped back to the GSK Clinical Unit. 3. Time of discharge may vary and will not be before all assessments have been completed 4. PD blood samples scheduled to be taken at the same time as a meal will be taken pre meal |
| --- |

# Study Population

## Number of Subjects

Approximately 16 subjects will be enrolled such that approximately 12 fully evaluable subjects complete critical assessments.

If subjects prematurely discontinue the study, additional subjects may be enrolled as replacement subjects at the discretion of the Sponsor in consultation with the investigator.

## Eligibility Criteria

### Inclusion Criteria

A subject will be eligible for inclusion in this study only if all of the following criteria apply:

1. T2DM men and women between 18 –70 years of age on stable dose of metformin
2. Subjects taking stable regimens of aspirin, ACE inhibitors, beta-blockers, calcium channel blockers, thyroid replacement hormone, and HMG-CoA reductase inhibitors (statins) will be allowed if their dose regimen(s) remain constant throughout the study period
3. HBA1C >6.5% <8.5%
4. BMI from 22.5 up to 37.5 kg/m2, inclusive
5. AST, ALT, alkaline phosphatase and bilirubin ≤ 3xULN
6. Has a normal ECG as determined by unit physician.
7. Capable of giving written informed consent, which includes compliance with the requirements and restrictions listed in the consent form.

### Exclusion Criteria

A subject will not be eligible for inclusion in this study if any of the following criteria apply:

- Medically unable or unwilling to discontinue current metformin therapy for as required by the protocol and remain off medication until the completion of Visit 3
- Past or present disease (other than T2DM) as judged by the Investigator, which may affect the outcome of this study. These diseases include, but are not limited to, cardiovascular disease, malignancy, hepatic disease, renal disease, haematological disease, neurological disease and endocrine disease.
- Subject is currently on bile acid sequestrant therapy.
- Gastrointestinal surgery or disease that would compromise the use of the EnteroTest

1. Fasting triglycerides >450mg/dL (>5.1 mmol/L)
2. Current or chronic history of liver disease, or known hepatic or biliary abnormalities (with the exception of Gilbert's syndrome or asymptomatic gallstones).
3. A positive pre-study drug/alcohol screen.
4. History of regular alcohol consumption within 6 months of the study defined as:

- An average weekly intake of >21 units for males or >14 units for females. One unit is equivalent to 8 g of alcohol: a half-pint (~240 ml) of beer, 1 glass (125 ml) of wine or 1 (25 ml) measure of spirits.

1. Use of prescription or non-prescription drugs, including vitamins, herbal and dietary supplements (including St John’s Wort) within 7 days (or 14 days if the drug is a potential enzyme inducer) or 5 half-lives (whichever is longer) prior to the first dose of study medication, unless in the opinion of the Investigator and GSK Medical Monitor the medication will not interfere with the study procedures or compromise subject safety.
2. Pregnant females as determined by positive (serum or urine) hCG test at screening or prior to dosing.
3. Lactating females.
4. Unwillingness or inability to follow the procedures outlined in the protocol.
5. Subject is mentally or legally incapacitated or unable to provide informed consent

# Data Analysis and Statistical Considerations

## Hypotheses and Treatment Comparisons

**Precision Estimation**

This study is designed to estimate the impact of temporary cessation of metformin treatment on faecal and serum bile acid concentrations, entero-endocrine peptide profiles and lipid metabolism. No formal hypotheses will be tested. Point estimates and corresponding 95% confidence intervals (CI) will be constructed for the mean levels of these parameters, their changes over time, and for the correlations between them and blood glucose and insulin.

## Sample Size Considerations

### Sample Size Assumptions

The sample size is based on feasibility. For any identified biomarker to be of practical use in future early phase studies it will have to be sufficiently sensitive that it can provide useful results in cohorts of approximately this size.

### Sample Size Sensitivity

The expected width of 95% CI for group means with 12 subjects is +/–0.62SD_b_ where SD_b_ is the between-subject standard deviation of the quantity of interest.

A sample size of 12 subjects is expected to detect “significant” correlations (i.e. different from zero) when the true correlation is greater than 0.56 in magnitude. Expected 95% CIs for a range of correlations are given in the table below.

| **Correlation** | **Expected 95% Confidence Interval** |
| --- | --- |
| 0.6 | (0.06, 0.87) |
| 0.7 | (0.23, 0.90) |
| 0.8 | (0.43, 0.94) |
| 0.9 | (0.68, 0.97) |

### Sample Size Re-estimation

No sample size re-estimation will be performed.

### Interim Analysis

No interim analysis is planned.

#### Safety Analyses

Safety data will be presented in tabular and/or graphical format and summarised descriptively.

#### Pharmacokinetic Analyses

Trough concentrations of metformin in plasma will be measured and pharmacokinetic analysis will be the responsibility of the Clinical Pharmacology Modeling and Simulation Department, GlaxoSmithKline. Plasma metformin concentration data will be analyzed by non-compartmental methods with WinNonlin Professional Version 5.2 or higher.

#### Pharmacodynamic/Biomarker Analyses

Bile acid measurements will be the responsibility of Investigative Preclinical Toxicology group within GlaxoSmithKline Ltd. Qualitative and quantitative measurements will be undertaken using a high performance liquid chromatography – mass spectrometry (LC-MS) based method. For quantitative measurements data will be obtain from comparison to authentic standards.

Bile acid quantitative measurements from blood serum and faeces will be presented in graphical and/or tabular form and will be summarised descriptively. All qualitative bile acid data will be presented in a tabular form and summarised descriptively. All data will be stored in the Archives of GlaxoSmithKline Pharmaceuticals, R&D.

Statistical analysis of the bile acid data and other primary and secondary endpoints will be the responsibility of Discovery Analytics, GlaxoSmithKline. Statistical analysis will include repeated measures models to estimate mean changes in endpoints over time (adjusted for any missing data), following appropriate transformations (e.g. log). Estimates of correlations between endpoints, and between changes in endpoints will also be produced, either non-parametric (Spearman rank) or from examining the variance-covariance matrices from multivariate repeated-measures models. Changes are expected to be largest between visits 1 and 3, so differences over this period will be investigated primarily.

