# ENDPOINT(S)

## Primary

During metformin wash out and when treatment reinstated, pharmacodynamic endpoints will include the following as data permit:

- 24h profiles of blood glucose and insulin
- Faecal and serum bile acid profiles
- Enteroendocrine peptide profiling including but not limited to tGLP-1, tGIP, and tPYY
- Serum lipid analysis including but not limited to fasting HDL and LDL cholesterol, fasting and prandial TGs, ApoA1, ApoB and ApoE

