# INVESTIGATIONAL PLAN

## Study Design/Schematic

## Discussion of Design

Because of the complexity of the entero-cellular kinetics of metformin, the period of time for investigation after metformin discontinuation or restart will be determined by monitoring the changes in fasting glucose. Thus, gastrointestinal and related markers are measured at the most informative times when there are visible changes in glucose. Subjects will be contacted daily by telephone by site staff from 7 days before Visit 1 until discharged following Visit 4.

**Visit 1** - At the first clinical unit admission (Visit 1) full PD profiles will be obtained whilst subjects are taking their usual dose of metformin.

**Visit 2 -** The first PD profiling during the metformin washout phase will be conducted 7 days after the first baseline visit to simulate the situation in early phase studies when T2DM subjects are washed off metformin for a fixed period of time.

**Visit 3 -** During the metformin washout, the site staff will continue to monitor patient progress daily and will schedule the subject for admission into the clinical unit for PD profiling (Visit 3) when the fasting CBG has increased by 25% or approximately 3 weeks has passed, whichever is sooner. If the average fasting CBG increases by the required amount within 7 days following Visit 1, then visit 3 will be eliminated and the subject will be asked to restart metformin after visit 2 is completed.

**Visit 4-** In the metformin re-start phase of the study, site staff will inform the subject when the fasting CBG has returned to the baseline level (determined at screening) and the subject will be scheduled for admission into the clinical unit for PD profiling. If the subject’s CBG has not returned to baseline level (approximate) within approximately 14-21 days, this visit will be scheduled once the subject has achieved clinically acceptable glycaemic control, in the opinion of the principal investigator.

The study will enrol approximately 16 subjects to ensure that12 fully evaluable T2DM patients complete the study. The study will consist of a screening visit and, 4 in-house study visits and a follow up visit, taking approximately 12 weeks to complete the study.

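### The prioritised Visit 1 to Visit 3 change mixes metformin withdrawal with time and visit-order effects, and the on-drug Visit 4 has no named role beside it

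*Protocol*

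**What the plan says.** Under Hypotheses and Treatment Comparisons the protocol sets its aim: "This study is designed to estimate the impact of temporary cessation of metformin treatment on faecal and serum bile acid concentrations", together with enteroendocrine peptides and lipid metabolism. It is an estimation study: "No formal hypotheses will be tested". For the mean levels, their changes over time and the correlations with glucose and insulin, "Point estimates and corresponding 95% confidence intervals (CI) will be constructed".

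There is one sequence for everyone: "All subjects will be assigned to an identical regimen in accordance with the treatment schedule outlined in Section 4.1". Visit 1 is on the usual metformin dose, Visits 2 and 3 are off it, and Visit 4 follows its re-introduction. Study Visits says that the assessments are the same at all four. The primary endpoints cover both phases: "During metformin wash out and when treatment reinstated, pharmacodynamic endpoints will include the following as data permit".

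The Pharmacodynamic/Biomarker Analyses section plans repeated-measures models for mean changes over time and then sets the priority: "Changes are expected to be largest between visits 1 and 3, so differences over this period will be investigated primarily". It names no reversal or on-off-on contrast.

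Discussion of Design schedules Visit 3 "when the fasting CBG has increased by 25% or approximately 3 weeks has passed, whichever is sooner". It drops Visit 3 if the rise occurs within 7 days of Visit 1. Visit 4 is scheduled when fasting glucose has returned to baseline or, if that has not happened within about 14–21 days, once control is judged clinically acceptable.

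**The concern.** With one arm and a fixed order, drug state and calendar time change together between Visits 1 and 3. The difference equals the withdrawal effect plus whatever else changed over that interval. Possible sources in the protocol are home diet that is encouraged to stay as usual but is not controlled, and Visit 1 being the subject's first overnight profiling stay with the EnteroTest string.

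The stated reason for the priority is the expected size of the change, which does not bear on whether the change can be attributed to metformin. Visit 4 does bear on that: a drug effect should reverse when metformin is resumed, whereas steady drift should continue. At stake is which bile acid, peptide and lipid markers are reported as responding to metformin withdrawal. A marker that merely drifts could receive a 95% CI excluding zero in the main comparison.

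**Working it through.** **Inputs.** From the protocol: n = 12 evaluable, 95% CIs, and the visit order and timing above. Not in the protocol, so assumed: within-subject errors independent across visits with SD σ_w, and the size of drift, for which a range is shown. Base timing: Visit 3 at day 21 and Visit 4 at day 42.

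**The plan's own precision figure.** Expected half-width for a mean = t(0.975, 11) × c4 / √12 = 2.201 × 0.9776 / 3.464 = 0.62 between-subject SD. This matches Sample Size Sensitivity. The same t-based method is used below, with one contrast value per subject and 11 degrees of freedom.

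**The two contrasts.**
- V3 − V1: variance 2σ_w², SE = √(2/12) = 0.408 σ_w, expected half-width 2.201 × 0.9776 × 0.408 = 0.88 σ_w.
- V3 − (V1 + V4)/2: variance 1.5σ_w², SE = √(1.5/12) = 0.354 σ_w, expected half-width 0.76 σ_w. The SE ratio is √0.75 = 0.866, so 13% smaller.

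**Bias under linear drift.** Let d be the drift over the 21 days from V1 to V3. V3 − V1 carries all of d. The on-off-on contrast carries d × (day of V3 − half the day of V4)/21. This is 0 at days 21/42, and d/6 in size if V4 comes 14 or 28 days after V3.

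**Share of trials with no drug effect whose 95% CI excludes zero** (noncentral t, noncentrality = bias/SE):

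| d (σ_w over 21 days) | V3 − V1 | On-off-on, days 21/42 | On-off-on, days 21/35 or 14/35 |
|---|---|---|---|
| 0.25 | 9% | 5% | 5% |
| 0.5 | 20% | 5% | 6% |
| 0.75 | 39% | 5% | 6% |
| 1.0 | 61% | 5% | 7% |

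For example, d = 0.5 gives noncentrality 0.5/0.408 = 1.22, hence 20%. In the 14/35 case d is still expressed per 21 days.

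**Same point as coverage.** With total drift of 0.1, 0.2, 0.3 or 0.5 of the SD at a single visit, and within-subject correlation 0.5 to 0.7, the nominal 95% CI from V3 − V1 covers the true withdrawal effect in about 94–93%, 90–87%, 84–77% and 65–47% of trials. On-off-on keeps 93–95% with V4 two to four weeks after V3.

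**Where on-off-on falls short.**
- First-visit shift of 0.5 or 1.0 σ_w at V1 only: V3 − V1 excludes zero in 20% or 61% of trials. On-off-on carries half the shift and gives 10% or 25%.
- Late V4 (42 days after a day-21 V3): the bias is d × (21 − 31.5)/21 = −d/2, again 10% or 25% at d = 0.5 or 1.0.
- Incomplete recovery, true effect 1 σ_w: with a recovered fraction r, the contrast estimates 1 − (1 − r)/2 of the effect. Full recovery gives 73% detection, against 61% for V3 − V1. At r = 0.75 it estimates 0.875 of the effect (62% against 61%), and at r = 0.5 it estimates 0.75 (49% against 61%).

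**V3 to V4 alone.** Its variance is 2σ_w² and linear drift biases it as much as V1 to V3. However, drift pushes both changes in the same direction while a reversible drug effect pushes them in opposite directions, so the pair is informative.

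**The case against.** Several stronger readings are tempting, and the protocol does not support them.

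- **That Visit 4 is left out of the analysis.** A priority is not an exclusion. Visit 4 is within the primary endpoints and can enter the repeated-measures model. What is missing is a named role in the main comparison.
- **That starting self-testing and daily calls drives the drift.** Both begin about 7 days before Visit 1, and the calls continue through Visit 4. Only continuing adaptation could matter. Listed co-medications must stay constant, and usual diet and exercise are encouraged, which also limits drift.
- **That the type I error is inflated.** No formal test is planned. The harm is a biased estimate and a CI with poor coverage.
- **That the primary objective as a whole is compromised.** That objective concerns relationships between glucose lowering and the markers. A shift common to all subjects leaves correlations between changes unaltered.
- **That V1 to V3 should be replaced.** The stated target is the impact of cessation, and averaging V1 with V4 brings re-introduction into the estimate. Nothing in the protocol shows that lipids or apolipoproteins recover as fast as glucose, and at 50% recovery the on-off-on contrast detects less. Visit 4 is timed by glucose recovery, so it is least informative for glucose itself.
- **That a sign-reversal rule would settle attribution.** The two changes share V3 and so are negatively correlated. With no effect and no drift, their signs oppose in 67% of simulated trials, and in 88% of those where the V3 − V1 CI excludes zero.

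These points narrow the finding. They do not remove the confounding in the mean changes, for which the protocol promises 95% CIs, and leaving a full list of contrasts to an analysis plan does not alter the priority fixed here.

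**Conclusion.** The point holds for the mean-change estimates and their CIs. The prioritised difference cannot separate withdrawal from time or visit order, and a visit that helps to do so is already collected but unnamed in that comparison. The size is unknown because the protocol gives no drift figure or within-subject SD. The 9–61% range rests on assumed linear drift of 0.25 to 1.0 σ_w over three weeks, independent errors and 12 subjects. At the low end the excess over 5% is small. The 5–7% for on-off-on requires V4 to lie about as far from V3 as V1 does.

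Three weeks is an upper bound for the interval: Visit 3 may come sooner or be dropped. The Study Rationale gives two weeks where Discussion of Design and Study Visits give about three, and these passages must be reconciled. A missing Visit 3 affects both contrasts alike.

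**What to change.** In Pharmacodynamic/Biomarker Analyses, keep the V1-to-V3 change and name two further estimates of equal priority from the same repeated-measures model: the V3-to-V4 change, and V3 minus the mean of V1 and V4. Give each a 95% CI. State that a marker's change will be attributed to metformin from these estimates and intervals read together, with no sign-reversal rule.

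State the limits in the same place. The on-off-on contrast is attenuated if a marker has not fully recovered by Visit 4. It removes only roughly linear drift with roughly equal spacing, only halves a first-visit effect, and is least informative for glucose because Visit 4 is timed by glucose recovery.

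The cost is a few sentences and two more reported estimates per endpoint. No visit, sample or subject is added.
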